# Effect of a multicomponent exercise programme (VIVIFRAIL) on functional capacity in frail community elders with cognitive decline: study protocol for a randomized multicentre control trial

**DOI:** 10.1186/s13063-019-3426-0

**Published:** 2019-06-17

**Keywords:** Multicomponent exercise, Frail, Gait impairment, Functional capacity, Cognitive impairment

## Abstract

**Background:**

The benefit of physical exercise in ageing and particularly in frailty has been the aim of recent research. Moreover, physical activity in the elderly is associated with a decreased risk of mortality, of common chronic illnesses (i.e. cardiovascular disease or osteoarthritis) and of institutionalization as well as with a delay in functional decline. Additionally, very recent research has shown that, despite its limitations, physical exercise is associated with a reduced risk of dementia, Alzheimer disease or mild cognitive decline. Nevertheless, the effect of physical exercise as a systematic, structured and repetitive type of physical activity, in the reduction of risk of cognitive decline in the elderly, is not very clear. The purpose of this study aims to examine whether an innovative multicomponent exercise programme called VIVIFRAIL has benefits for functional and cognitive status among pre-frail/frail patients with mild cognitive impairment or dementia.

**Methods/design:**

This study is a multicentre randomized clinical trial to be conducted in the outpatient geriatrics clinics of three tertiary hospitals in Spain. Altogether, 240 patients aged 75 years or older being capable of and willing to provide informed consent, with a Barthel Index ≥ 60 and mild cognitive impairment or mild dementia, pre-frail or frail and having someone to help to supervise them when conducting the exercises will be randomly assigned to the intervention or control group. Participants randomly assigned to the usual care group will receive normal outpatient care, including physical rehabilitation when needed. The VIVIFRAIL multicomponent exercise intervention programme consists of resistance training, gait re-training and balance training, which appear to be the best strategy for improving gait, balance and strength, as well as reducing the rate of falls in older individuals and consequently maintaining their functional capacity during ageing.

The primary endpoint is the change in functional capacity, assessed with the Short Physical Performance Battery (1 point as clinically significant). Secondary endpoints are changes in cognitive and mood status, quality of life (EQ-5D), 6-m gait velocity and changes in gait parameters (i.e. gait velocity and gait variability) while performing a dual-task test (verbal and counting), handgrip, maximal strength and power of the lower limbs as well as Barthel Index of independence (5 points as clinically significant) at baseline and at the 1-month and 3-month follow-up.

**Discussion:**

Frailty and cognitive impairment are two very common geriatric syndromes in elderly patients and are frequently related and overlapped. Functional decline and disability are major adverse outcomes of these conditions. Exercise is a potential intervention for both syndromes. If our hypothesis is correct, the relevance of this project is that the results can contribute to understanding that an individualized multicomponent exercise programme (VIVIFRAIL) for frail elderly patients with cognitive impairment is more effective in reducing functional and cognitive impairment than conventional care. Moreover, our study may be able to show that an innovative individualized multicomponent exercise prescription for these high-risk populations is plausible, having at least similar therapeutic effects to other pharmacological and medical prescriptions.

**Trial registration:**

ClinicalTrials.gov, NCT03657940. Registered on 5 September 2018.

**Electronic supplementary material:**

The online version of this article (10.1186/s13063-019-3426-0) contains supplementary material, which is available to authorized users.

## Background

The progressive ageing of the population and the challenges surrounding the care of elderly people have become an emergency for all health systems. The aged population has resulted in an increase in the activity of health and social services, and the needs of this population are completely different compared to those of similar age groups 50 years ago. Nowadays, it is time for a clinical transition in health systems, moving from disease management to a more functional perspective, around the principles of integrated, coordinated, continued and patient-centred care [1]. In this context, the World Health Organization recently stated that health-related policies should be considered from the perspective of the elderly person’s functional capacity (intrinsic capacity) rather than the disease or comorbidity experienced at a single point in time [2].

Frailty is a clinical syndrome defined by vulnerability and an increased risk of the individual to develop negative health-related events as disability and/or mortality under external stressors factors [3]. The frail phenotype pays attention to five domains (nutritional status, energy, physical activity, mobility and strength), and five criteria have been stablished (one per each domain: weight loss, exhaustion, leisure-time activity, gait speed and grip strength, respectively) [4] to identify older persons at high risk of numerous adverse outcomes [5, 6]. Some cross-sectional studies show the relation between frailty, mild cognitive impairment (MCI) and dementia, but the longitudinal relation is uncertain. Probably, the relation between cognitive impairment and frailty [7] in some cases is strong and bidirectional, since they share common pathophysiological bases and the same outcomes as hospitalization, falls, fractures, disability, institutionalization and mortality. Recently, the frailty Toledo study of aging has showed that cognitive impairment and muscular strength have a direct proportional relationship [8]. Therefore, dementia shares part of the same characteristics that can be found in the frail phenotype like subtle gait impairments (slow gait velocity and increase gait variability) and poor physical activity (Fig. 1).

**Fig. 1 Fig1:**
[figure not shown]
Proposed relation, sharing mechanisms and similar outcomes between frailty, mild cognitive impairment (MCI) and dementia

The regular practice of physical exercise constitutes an inexpensive and healthy way of preventing and treating several illnesses related to the cardiovascular system and a sedentary lifestyle. Physical exercise programmes have been shown to be a novel “prescription tool” to prevent or delay the appearance of disability [9], to diminish healthcare costs [10] and to delay premature mortality [11, 12]. In the context of the ageing population, the performance of physical exercise can be considered the most effective intervention to delay disability and adverse events that are usually associated with frailty and vulnerable ageing. In some studies, exercise has shown even more positive results in terms of mortality from different diseases and chronic conditions than poly-pills for cardiovascular prevention [13]. Physical exercise, as an individual intervention, is one of the most important components in improving the functional capacity of frail seniors, and muscle strengthening in particular should be at the forefront of the treatment [14].

The benefit of physical exercise in ageing and particularly in frailty has been the aim of recent research. Moreover, physical activity in the elderly is associated with a decreased risk of mortality, of common chronic illnesses (i.e. cardiovascular disease or osteoarthritis) and of institutionalization as well as with a delay in functional decline. Additionally, very recent research has shown that, despite its limitations, physical exercise is associated with a reduced risk of dementia, Alzheimer disease or mild cognitive decline [15, 16]. Nevertheless, the effect of physical exercise as a systematic, structured and repetitive type of physical activity, in the reduction of risk of cognitive decline in the elderly, is not very clear. In this context, the most beneficial type of physical exercise is called multicomponent exercise [17–20]. This type of programme combines strength, resistance (aerobic), balance and flexibility training and has been shown to result in great improvements in functional capacity, which is a key point in maintaining independence in instrumental and basic activities of daily living.

Considering the relation between frailty and cognition previously mentioned (Fig. 1), it makes sense that those interventions proved to be effective in frail elderly people could be also effective in the elderly with cognitive impairment, and vice versa. Although there are still few studies, some of them show how resistance exercise programmes during 12 weeks in older adults not only induce improvements in gait velocity but also improvements in executive functions [21] which are directly related to fall risk [22]. Additionally, recent research [23] has shown that, despite its limitations, multicomponent exercise can be one of the best approaches to improving functional capacity and executive functions and to decreasing fall risk and cognition in frail institutionalized elderly with cognitive impairment and dementia [22]. Other authors have found similar results in terms of reversing the frailty status and cognitive improvements in community-dwelling elderly without basal cognitive impairment [24].

In this context, the purpose of this study aims to examine whether an innovative multicomponent exercise programme called VIVIFRAIL [25–27] has benefits for functional and cognitive status among pre-frail/frail patients with MCI or dementia. VIVIFRAIL was developed by world experts in the field of physical exercise and frailty, and is considered an important step towards the novel era of precise prescription of physical activity [26, 27]. Recently, it has been proven safe and effective to reverse the functional decline associated with acute hospitalization in very old patients [28]. This programme is a significant step towards an individualized physical exercise programme [27] according to the functional capacity of each elderly person and includes specific recommendations on doses (intensity, volume and frequency), similar to other treatments applied to vulnerable populations, such as frail elderly individuals with cognitive complaints.

## Methods

### Study design and setting

This study is a multicentre randomized clinical trial to be conducted in the outpatient geriatrics clinics of three tertiary hospitals in Spain. Geriatric clinics are part of routine geriatric clinical work and normally patients come from primary care or other specialities. Patients who meet the inclusion criteria will be randomly assigned to the intervention or control group. Prior to randomization, the attending geriatrician will review the absolute and relative contraindications to participate in the exercise programme and will provide general information about the study. Patient recruitment will begin with the normal visit of the patient to the clinic assessing for inclusion criteria and obtaining informed consent. Later on, subjects will be randomly assigned (as explained in the following) to either the intervention or the control group. The researcher who decides whether the patient is assigned to the intervention or control group will not be the attending geriatrician. Patients or their relatives (if the patient has dementia) will be informed of the random inclusion in one group but will not be informed regarding to which group they belong. The data for both the intervention group and the control group will be obtained at three different times: at baseline and at the 1-month and 3-month follow-up. We will perform two telephone calls (15 days and 2 months after baseline) to assess adherence and reinforce the protocol applied. In addition, in order to improve the adherence of the exercise programme, participants in the intervention group will record a diary that will be reviewed during follow-up. After randomization, the research team (physiotherapist, sport science specialist and geriatrician) will together perform the baseline measurement and follow-up visits of functional, pharmacological, comorbidity and cognitive assessment, as well as of mobility and strength evaluations (Table 1). The multidisciplinary research team have well-known previous experience in functional geriatric assessment and in the prescription of exercise in frail aged participants in different clinical settings [25, 26, 28].

**Table 1 Tab1:** Schedule for the different primary and secondary variables for the participants of the study

Measure	Screening	T1 Baseline	T2 1 month	T3 3 months
Primary outcome				
Short Physical Performance Battery (SPPB)		X	X	X
Secondary outcomes				
Barthel Index	X		X	X
Frailty according to the Fried criteria	X			
Montreal Cognitive Assessment (MOCA)—only for mild cognitive impairment	X		X	X
Categorical scale of pain		X		X
Geriatric Depression Scale of Savage (GDS)		X		X
Minimental Cognitive Exam (MEC-Lobo)		X	X	X
Gait velocity test (GVT)		X	X	X
Dual task (verbal and counting GVT)		X	X	X
Maximal isometric force of handgrip, knee extension and hip flexion		X	X	X
Isaacs Set Test		X		X
Quality of Life (EQ-5D)		X		X
Trail Making Test (TMT—Part A)		X	X	X
1RM (leg press)		X	X	X
Muscle power at 50% 1RM in leg press		X	X	X
Drugs, geriatric syndromes and psycho-behavioural symptoms		X		X
Cumulative Illness Rating Scale for Geriatrics (CIRS-G)		X		
Functional Activities Questionnaire (FAQ)		X	X	X
Mini Nutritional Assessment (MNA)		X		
Acceleration data: gait kinematic parameters (regularity, variability, cadence), Five Times Sit to Stand Test (peak power, impulse) and balance parameters (power spectrum, area)		X	X	X
Rate and risk of falls		X	X	X
Mortality		X	X	X
Admission and readmission to hospital		X	X	X
Institutionalization		X	X	X

Basic sociodemographic data of the participants will be collected in the baseline visit. All adverse events, including those related to exercise such as muscle pain, fatigue and general aches and pains, will be recorded in an “adverse events diary” during follow-up visits and telephone calls by the training and testing staff, and by self-report during the study period. The study flow diagram is shown in Fig. 2. The time at which different variables (primary and secondary) will be measured is presented in Table 1. The protocol employs relevant standard protocol items for clinical trials according to the SPIRIT 2013 statement (Additional file 1) [29] and follows the CONSORT statement [30] for transparent reporting. The trial is registered at ClinicalTrials.gov (identifier number iNCT03657940), and the status is recruitment.

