### Randomization and blinding

Participants in the study will be randomized (www.randomizer.org) into an intervention group and a usual care group (control group) following a simple randomization procedure, in a 1:1 ratio without restriction. Participants will be explicitly informed and reminded not to discuss their randomization assignment with the assessment staff. The assessment staff will be blinded to the participants’ groups as well as to the main study design and to what changes in study outcomes we expect to occur in either group.

It will not be possible to conceal the group assignment from the staff involved in the training of the intervention group. Patients (or their families) will be informed of their random inclusion in one group but will not be informed regarding to which group they belong.

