#### Secondary outcomes

Loss of handgrip in the dominant hand is a useful tool for the measurement of functional capacity. This characteristic is a strong predictor of disability, morbidity and mortality as well as one of the components of Fried’s frailty phenotype [4]. Furthermore, the functional status of patients will also be assessed at recruitment with the Barthel Index [37], an international and validated tool of disability. The score ranges from 0 (severe functional dependence) to 100 (functional independence). At baseline, gait ability will be assessed using the 6-m gait velocity test (GVT). Starting and ending limits will be marked on the floor with tapelines for a total distance of 8 m. Participants will be instructed to walk at their self-selected usual pace for two attempts. The best result of both trials will be registered. The first and last metre, considered the warm-up and deceleration phases, respectively, will not be included in calculations of the gait assessment. Dual-task conditions (gait evaluation during the simultaneous performance of a cognitive task) have recently been recognized as a sensitive assessment method for interactions among cognition, gait, falls and frailty. Changes in gait parameters (i.e. gait velocity and gait variability) while performing a dual-task test (dual-task cost) may be early predictors of fall risk [38, 39] and may be useful tools for functional evaluations in frail older patients. Exercise can modify the dual-task cost and, consequently, the fall risk and functional capacity [40]. The dual-task paradigm [37] will be used in the 6-m habitual GVT. Two trials will be conducted to assess gait velocity while the patient is performing a verbal or counting task (verbal GVT and arithmetic GVT, respectively). During the verbal dual-task condition (verbal GVT), we will measure gait velocity while participants are naming animals aloud. During the arithmetic dual-task condition (arithmetic GVT), we will assess gait velocity while participants are counting backwards aloud from 100 in ones. The cognitive score will be measured by counting the number of animals named (dual-task with verbal performance) or determining how many numbers were counted backwards (dual-task with arithmetic performance). Isometric upper limb (dominant hand grip) and lower limb (right knee extensors and hip flexors) muscle strength will be measured using a manual dynamometer. Maximal dynamic strength will be assessed using the 1RM test in the bilateral leg press exercise using exercise machines (Matrix, Johnson Health Tech, Ibérica, S.L., Torrejón de Ardoz, Spain; and Exercycle S.L., BH Group, Vitoria, Spain). In the first assessment, the subjects will warm up with specific movements for the exercise test. Each subject’s maximal load will be determined in no more than five attempts, with a 3-min recovery period between attempts. After the 1RM values are determined, the subjects will perform 10 repetitions at maximal velocity and at intensities of 50% of 1RM to determine the maximum power (W) and the loss of power during the 10 repetitions in the leg press exercise [41]. The power will be recorded by connecting a velocity transducer to the weight plates (T-Force System, Ergotech, Murcia, Spain). During all neuromuscular performance tests, strong verbal encouragement will be given to each subject to motivate them to perform each test action as optimally and rapidly as possible. Distribution of the training sessions throughout the day should minimize cumulative fatigue and help to maintain adherence. Adherence to the exercise programme will be documented in an individual daily log of the sessions. Changes in cognitive-affective status after the intervention will be measured using the Spanish validated versions of the Minimental Cognitive Exam (MEC-Lobo) [42] in the case of dementia and the MOCA [43] in the case of MCI. The Yesavage GDS [44] and Trail Making part A [45] will be performed to assess depression and executive dysfunction. During functional tasks (such as balance, gait and rising from a chair) and cognitive evaluations (dual tasking), an inertial sensor unit (IU) will be attached over the lumbar spine (L3) to record the acceleration data in control and intervention participants [46, 47]. Primary and secondary variables are presented in Table 1.

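### Adverse events may be captured unequally between arms, because unblinded training staff and a reviewed diary are attached to the exercise arm

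*Protocol article*

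**What the plan says.** Methods, Study design and setting, covers adverse events in one sentence. Its scope is "All adverse events, including those related to exercise such as muscle pain, fatigue and general aches and pains", and the events are entered in an adverse events diary "during follow-up visits and telephone calls by the training and testing staff, and by self-report during the study period". Nothing in that sentence limits it to one arm.

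Three other statements bear on who supplies these records:

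- Randomization and blinding says that allocation cannot be concealed from "staff involved in the training of the intervention group". The assessment staff, by contrast, are to be blinded.
- Study design and setting says that "participants in the intervention group will record a diary that will be reviewed during follow-up". The stated purpose is "in order to improve the adherence of the exercise programme". Secondary outcomes adds: "Adherence to the exercise programme will be documented in an individual daily log of the sessions".
- Study design and setting also says: "We will perform two telephone calls (15 days and 2 months after baseline) to assess adherence and reinforce the protocol applied". No arm is named.

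The section on the usual care group describes normal outpatient care and no training contact. In Table 1, "Rate and risk of falls" is a secondary outcome at baseline, 1 month and 3 months. Data collection at those times is stated for both groups.

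**The concern.** A between-arm comparison of adverse events is interpretable only if an event has about the same chance of being recorded in either arm. Here one of the two named types of recorder is tied by its job to the exercise arm and knows the allocation. Only that arm has a written record that is gone through at follow-up, and going through exercise sessions with a patient can prompt mention of an ache or a fall. The calls, which are also an occasion for recording events, have a purpose that fits the exercise arm more naturally than usual care.

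The population makes this matter more. Participants are selected for mild cognitive impairment or mild dementia, so self-report without a prompt is a weak source, and extra prompting in one arm could make more difference than it would in other patients. The adverse events named as examples (muscle pain, fatigue, aches) are also those that someone supervising exercise would look for.

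At stake is the safety comparison: the programme could appear to cause more symptoms because more were written down. Unequal capture of this kind cannot be repaired at analysis.

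**Working it through.** The article gives no fall or adverse-event rate and no capture rate, so there is no event figure to reproduce. Its one design figure, the SPPB sample size, reproduces closely. With SD 2.5 × √(1 − 0.5²) = 2.165, two-sided α of 5% and 90% power, n = 2 × (2.165 × (1.960 + 1.282))² = 98.5, so 99 per group against 101 stated. Allowing for 15% loss, 101/0.85 gives 119 against 120 stated. That figure does not depend on adverse-event recording.

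**Step 1: sources by arm, as the text gives them.**

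| Source | Exercise arm | Usual care |
|---|---|---|
| Visits at 1 and 3 months | yes | yes |
| Self-report | yes | yes |
| Calls at 15 days and 2 months | yes | arm not stated; purpose is adherence |
| Training staff as recorders | yes, unblinded | no training contact described |
| Diary reviewed at follow-up | yes, for adherence | none described |

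Two sources are common, one is unclear, and two are described only for the exercise arm. Of those two, training staff are an explicit event source. The diary is one only indirectly, through what its review may prompt.

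**Step 2: what unequal capture would do.** The formula is:

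apparent rate ratio = true rate ratio × (capture in exercise arm ÷ capture in control arm)

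All capture values below are assumptions.

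| True ratio | Capture, exercise v control | Apparent ratio |
|---|---|---|
| 1.00 | 70% v 70% | 1.00 |
| 1.00 | 80% v 70% | 0.80/0.70 = 1.14 |
| 1.00 | 90% v 70% | 0.90/0.70 = 1.29 |
| 1.00 | 90% v 60% | 0.90/0.60 = 1.50 |
| 0.80 | 70% v 70% | 0.80 |
| 0.80 | 80% v 70% | 0.80 × 1.143 = 0.91 |
| 0.80 | 90% v 70% | 0.80 × 1.286 = 1.03 |

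Over 80–90% in the exercise arm and 60–80% in controls, a true ratio of 1.0 appears as anything from 0.80/0.80 = 1.00 to 0.90/0.60 = 1.50.

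**Step 3: direction.** The ratio falls below 1 if the unblinded trainers record less than is recorded for controls. For example, 70% v 80% gives 0.70/0.80 = 0.88. More prompts in the exercise arm make a ratio above 1 the likelier result, but the text does not exclude the reverse.

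**The case against.** The strongest reply is that the recording sentence names occasions, not arms. Training staff are listed as recorders at visits and calls, not at exercise sessions. Visits take place in both arms and self-report is open to everyone. The calls are not restricted to one arm. Study design and setting has the research team perform follow-up visits together, with no split by arm, and nowhere says that training staff never see controls. Regular staff contact at exercise sessions is not described, since each participant has a helper to supervise them. The diary is an adherence log and is distinct from the adverse events diary. The statistics section sets out no between-arm test of adverse events. The exact wording of event questions is a detail that a journal article commonly leaves to the full protocol.

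Most of this stands, and it rules out two stronger readings. A reader might infer that event rates are shown to be biased against the intervention. The text shows a risk of unequal capture, not its presence, size or certain direction. A reader might also infer that the falls rate cannot be interpreted. Falls are a Table 1 outcome on the same schedule in both arms, with no additional falls channel stated for the exercise arm. Nothing says that a fall learned from training staff or from the diary is counted in that outcome, although nothing says that it is not.

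The reply does not remove the asymmetry that the text itself states: recorders attached to one arm who cannot be blinded, a reviewed record in that arm only, and event-recording calls described by an adherence purpose.

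**Conclusion.** The point holds as a minor one. Following the article as written, adverse events may be ascertained unequally, probably with more recorded in the exercise arm. The apparent ratios of 1.00 to 1.50 illustrate assumed capture rates and are not an estimate; with equal capture there is no distortion. The conclusion rests on two assumptions: that training staff have more contact with intervention participants than with controls, and that reviewing the diary can prompt event reports. Both are plausible, and neither is stated. The falls outcome is touched only if falls learned through these routes are counted in it. The SPPB analysis and the sample size are unaffected.

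**What to change.** State that the blinded assessment staff ask one identical set of adverse-event and falls questions of the patient and the helper, in both arms, at the calls at 15 days and 2 months and at the 1-month and 3-month visits. Say explicitly that both arms are called. Base between-arm comparisons of adverse events and falls only on events elicited this way. List events learned only through training staff or the exercise diary separately, as safety data for the intervention arm.

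Two practical details protect the blinding. Word the questions without reference to exercise, and ask them after the performance tests and before any adherence or diary discussion, which another member of staff should handle.

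The cost is a short common form, a wording change and some division of work at calls and visits. The calls, visits and helpers are already in the design. The small downside is that some events leave the comparative table, though they are still reported. The change helps only from the time it is made: recruitment began in September 2017, so events already collected under the present arrangement should be identified as such.

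### Assessors are declared blind, but the written follow-up procedures give testing staff tasks that can reveal allocation, and nothing separates diary review and adherence calls from SPPB scoring

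*Protocol article*

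**What the plan says.** All references are to the protocol article.

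- **Randomization and blinding.** "The assessment staff will be blinded to the participants’ groups as well as to the main study design", and also to the changes expected in either group. The only staff from whom allocation is said to be impossible to conceal are those who train the intervention group. Participants are told, and reminded, not to talk about their assignment with the assessors.
- **Study design and setting, adverse events.** "All adverse events, including those related to exercise such as muscle pain, fatigue and general aches and pains" are to be recorded in an adverse events diary "during follow-up visits and telephone calls by the training and testing staff", and by self-report.
- **Study design and setting, contacts between visits.** There will be "two telephone calls (15 days and 2 months after baseline) to assess adherence and reinforce the protocol applied".
- **Study design and setting, adherence diary.** "participants in the intervention group will record a diary that will be reviewed during follow-up". No reviewer is named.
- **Study design and setting, who measures.** After randomization, "the research team (physiotherapist, sport science specialist and geriatrician) will together perform the baseline measurement and follow-up visits", covering functional and cognitive assessment, mobility and strength.
- **Table 1.** The SPPB, the primary outcome, is scored at baseline, 1 month and 3 months.

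**The concern.** One arm follows a 12-week exercise programme and the other receives usual care. Participants are not to be told their group, but most will be able to work it out. Blinding of the assessor is therefore the main protection against detection bias in a primary outcome that staff administer and score. The blinding section promises that protection. The design section then assigns testing staff to a task that asks about the effects of exercise, alongside training staff who are acknowledged to be unblinded. It also places adherence discussion and review of a one-arm diary inside follow-up, without saying that the SPPB assessor is kept away from them.

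At stake is whether a difference in SPPB at 1 or 3 months can be read as an effect of the programme, free of the assessor's knowledge of the group.

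**Working it through.** **1. Comparing the sections**

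| Task in Study design and setting | Who does it, as written | Can it disclose the arm? | Compatible with the blinding section? |
|---|---|---|---|
| Recording adverse events, including exercise-related ones, at visits and calls | Training and testing staff | Can suggest it; aches and fatigue also occur under usual care | Hard to square with blindness to the main study design; puts blindness to group at risk |
| Calls at 15 days and 2 months on adherence | Caller not named for adherence; testing staff are among those recording adverse events on calls | Yes, if adherence to exercise is discussed | Only if the caller does not score that participant |
| Review of the diary | Reviewer not named; the research team performs the follow-up visits | Yes, since only one arm keeps it | Only if the reviewer does not score that participant |
| Follow-up assessments | One research team, acting together | Not by itself | Only if roles within the team are separated |

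The first row is a conflict in the text, because testing staff are named. The other rows are exposures that the text leaves open.

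**2. Timing**

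The order of tasks within a visit is not stated, so the text does not show that the SPPB is scored after a same-day diary review. The order between contacts is stated or follows from the schedule:

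- The 15-day call comes before the 1-month SPPB.
- The 2-month call, and any diary review at 1 month, come before the 3-month SPPB.

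If the person making the call or reviewing the diary also scores the SPPB, the exposure precedes a later scoring whatever the order within a visit.

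**3. Illustration of what a bias would do**

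Inputs from Statistics and sample size: SD 2.5, pre–post correlation 0.5, ANCOVA, alpha 5%, power 90%, difference 1 point, 101 per group, 15% loss, 120 per group.

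The plan's own figure first, taking alpha as two-sided:

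- ANCOVA residual SD = 2.5 × √(1 − 0.5²) = 2.165.
- n per group = 2 × (1.96 + 1.282)² × 2.165² / 1² = 98.5, so 99, against the stated 101.
- 101 / 0.85 = 118.8, so 119, against the stated 120.

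The sample size is reproduced closely and is not in dispute.

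Completers per group: 120 × 0.85 = 102. Standard error of the group difference: 2.165 × √(2/102) = 0.303.

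Suppose there is no true effect, but knowledge of the group shifts the measured difference by b points. The two-sided rejection probability is P(|Z + b/0.303| > 1.96):

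| Assumed b (SPPB points) | Share of the 1-point target | False-positive rate |
|---|---|---|
| 0 | 0% | 5.0% |
| 0.2 | 20% | 10.1% |
| 0.25 | 25% | 13.1% |
| 0.3 | 30% | 16.8% |
| 0.5 | 50% | 37.8% |

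The values of b are assumptions. Nothing in the article supports a particular one.

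**The case against.** Several points on the other side are sound.

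- **Adverse events.** Recording covers all events, hence both arms. Muscle pain, fatigue and aches are common in frail people of 75 or older, and controls may receive physical rehabilitation. A blinded assessor could record them without learning the arm. A reader might infer that the recording necessarily reveals allocation, or that the statements cannot all hold together. The text supports only that it can reveal it.
- **Diary and calls.** A reader might infer that the SPPB assessors review the diaries. The article does not say so. It names neither the reviewer nor the adherence caller, and it does distinguish training from assessment staff. These tasks may already belong to trainers.
- **Visit order.** A reader might infer that disclosure comes before SPPB scoring at the same visit. No order is given.
- **Encouragement.** The statement that "strong verbal encouragement will be given to each subject" concerns the neuromuscular tests described with it, which are secondary strength and power outcomes. It applies to every participant and is no evidence about the SPPB.
- **Safeguard.** Participants are asked not to disclose their assignment. This counts for something. However, all have mild cognitive impairment or mild dementia, and the request does little when staff themselves raise exercise effects or adherence.
- **Condensed article.** Division of tasks is detail that a full protocol may hold. That answers the unnamed diary reviewer and caller. It does not answer the sentence that names testing staff, which conflicts with the blinding section as printed.

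**Conclusion.** The point holds in limited form. The article declares assessors blind to group and to the main study design, yet it assigns testing staff to record exercise-related adverse events. It also leaves adherence calls, one-arm diary review and team-run follow-up assessments unseparated from SPPB scoring. As written, these procedures can unblind the SPPB assessor. The text does not show that they do so for every participant.

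The conclusion about the later SPPB assessments rests on one condition that the article neither states nor excludes: that the person who handles a call, diary or adverse-event enquiry also scores that participant.

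The size of any bias is unknown. The range of 10% to 38% for the false-positive rate only restates an assumed bias of 0.2 to 0.5 points with a standard error of 0.303, and it is not evidence of severity. The sample size is unaffected. Any concern about encouragement is confined to the secondary strength and power tests.

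**What to change.** Reconcile Study design and setting with Randomization and blinding, so that:

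1. At 1 and 3 months the assessor completes the SPPB and the other performance tests before any discussion of adverse events, diary or adherence, and without access to those records.
2. Diary review and the 15-day and 2-month adherence calls go to existing team members who do not score that participant's outcomes.
3. Adverse events are collected in the same way in both arms, either after testing or by a team member who does not score that participant. They should not pass to training staff alone: those staff are described only for the intervention group, and ascertainment could then differ between arms.
4. Optionally, the assessor records a guess of allocation after the 3-month SPPB.

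**Cost.** Some reallocation of tasks within the existing team, a visit-order rule and, if wanted, one case report form item. The article describes no site staffing, so each centre must confirm that it can separate the roles. Trial status gives recruitment as open since September 2017, with the target expected by September 2019. The change therefore protects only the remaining visits, and the report should say which assessments came before it.
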